### 11.2 Statistics Analysis Plan

The “full analysis set” is defined as any subject who receives any amount of the study medication with initial information on the primary endpoint. The full analysis set will be the primary analysis set for efficacy to use an *intention-to-treat* patient population.

For the primary endpoint, one-way analysis of variance across the 2 groups will be performed with calculating the p-value using the Student’s t-test. The p-value will be significant at a two-sided significant level of 5%. Both the p-value and confidence intervals will be used to determine whether our results are statistically significant or not. The paired t-test or Wilcoxon signed-rank test will be performed to compare before and after the intervention within each group. The chi-squared test will be used to assess the frequency of AE. The treatment compliance rate will be calculated and compared using Fisher’s exact test. The JMP version 11.2.0 software (SAS Institute, Cary, NC, USA) will be used for all statistical analyses.

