## 7.3 Criteria for discontinuation

If the patient meets any of the following criteria, the investigator will discontinue the protocol treatment. The "date of discontinuation" is the date when the physician in charge decides to discontinue, not the date when the event that is the reason for discontinuation occurs. Discontinuation cases in (1) through (3) will continue to be observed as long as possible.

- (1) When a grade 3 or more severe AE according to the NCI-CACTE version 4.0 occurs
- (2) When oral compliance with the study medication is less than 80%
- (3) When the patient requests discontinuation of the study
- (4) When continuous medical examination becomes challenging due to patient's relocation, change in hospital or busy schedule, etc.
- (5) When the patient turns out to be ineligible for the trial after enrollment
- (6) When the physician in charge of the study determines that the continuation of the study treatment is not possible for any other reasons

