### 9.2.2 Clinical findings

Patient's QOL and clinical symptoms will be investigated using the PAC-QOL/PAC-SYM/CSS questionnaires. The presence of constipation will be assessed using the Rome IV criteria and stool shape will be assessed using the Bristol Stool Form Scale. Patients will be randomized after study enrollment and will be seen at 2 weeks ( $\pm 7$  days), 12 weeks ( $\pm 14$  days) and at the time of discontinuation ( $\sim +2$  days) and the PAC-QOL/PAC-SYM/CSS/Rome IV/ Bristol Stool Form Scale/SMBs questionnaires will be performed at the visits.

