## 10. Study endpoints

### 10.1 Primary Endpoint

The change in JPAC-QOL from baseline at 2 weeks

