## 11. Statistical Analysis

### 11.1 Planned Sample Size

Our retrospective analysis of magnesium oxide/naldemedine in 10 OIC patients at

Yokohama City University Hospital showed a mean JPAC-QOL change of -1.19 in the

naldemedine group and -0.76 in the magnesium oxide group. We decided to perform

sample size calculation to attain a relevant number for proper analysis of variance F-test based on these data. Assuming mean changes in the JPAC-QOL score in the naldemedine group and magnesium oxide group to be -1.19 and -0.76, respectively, with a common standard deviation of 0.76, 51 patients are needed in each group to reach 90% statistical power with a two-sided significance level of 5%. To compensate for any dropout, we proposed to increase the sample size to 60 per group. To reach this sample size, a total of 120 patients in the study are needed.

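### The full analysis set is labelled intention-to-treat but leaves out undosed patients, and the protocol does not secure a week-2 score after every reason for stopping

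*Protocol*

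**What the plan says.** - **Analysis set (11.2).** The full analysis set is "any subject who receives any amount of the study medication with initial information on the primary endpoint". The same section states that "The full analysis set will be the primary analysis set for efficacy" and describes this as using an intention-to-treat population.
- **Endpoint and test (10.1, 11.2).** The primary endpoint is "The change in JPAC-QOL from baseline at 2 weeks". For its analysis, "one-way analysis of variance across the 2 groups will be performed with calculating the p-value using the Student’s t-test".
- **Follow-up after stopping treatment (7.3).** Six reasons are listed: (1) an adverse event of grade 3 or worse, (2) compliance below 80%, (3) patient request, (4) relocation, change of hospital or similar, (5) "When the patient turns out to be ineligible for the trial after enrollment", and (6) any other reason in the physician's judgement. Then: "Discontinuation cases in (1) through (3) will continue to be observed as long as possible". Nothing equivalent is said for (4) to (6).
- **Visits (9.2.2).** Patients are seen at 2 weeks (±7 days), at 12 weeks (±14 days) and at discontinuation (up to 2 days later). The PAC-QOL and the other "questionnaires will be performed at the visits". The discontinuation visit is not limited by reason.
- **Allowance for loss (11.1).** The calculation gives 51 per group, and then: "To compensate for any dropout, we proposed to increase the sample size to 60 per group".
- **Masking (6.3, 6.5).** Patients and physicians are not masked. The data center sends the drug name to the investigator when the patient is found eligible.

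**The concern.** An intention-to-treat comparison keeps every randomised patient in the assigned arm, so that what happens after allocation cannot select who is compared. Two provisions work against that here.

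First, membership of the set depends on taking at least one dose. Because the arm is known before the first tablet, a decision not to start can depend on the arm, and that patient then leaves the analysis. Membership also depends on 'initial information', which could mean a baseline score or a first score on treatment. These are different populations.

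Secondly, whether an outcome is pursued after treatment stops depends on why it stopped. Reasons (5) and (6) arise after allocation, and (6) is an open judgement by a physician who knows the arm. If patients who stop early for these reasons differ from the rest, and do so unequally by arm, the comparison of means is distorted while still carrying the intention-to-treat label. A later analysis plan can choose how to handle missing scores, but it cannot recover scores that were never sought.

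**Working it through.** **Step 1. The plan's own figures.** Inputs from 11.1: mean changes −1.19 and −0.76 (difference 0.43), SD 0.76, two-sided 5%, 51 per group raised to 60.

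- The allowance reproduces as a 15% loss: 1 − 51/60 = 0.15, and 51/0.85 = 60. That is up to 9 patients per arm.
- The 51 itself does not reproduce at 90% power: 2 × (1.960 + 1.282)² × 0.76² / 0.43² ≈ 65.7, so 66 per group (67 by the exact t-test). With 51 the exact t-test has 80.8% power. This is a separate matter, and it is noted here only because it leaves less room for lost scores.

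**Step 2. Who has a week-2 score under the text as written?** The week-2 window of ±7 days runs from day 7 to day 21.

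| Patient | What the protocol secures |
|---|---|
| Randomised, never dosed | Outside the full analysis set |
| Stops after the week-2 assessment | Week-2 score already taken |
| Stops before week 2, reasons (1) to (3) | Observation continues as far as possible |
| Stops for (4) to (6), discontinuation visit on day 7 to 21 | A score inside the week-2 window, but no rule on whether it counts |
| Stops for (4) to (6), discontinuation visit before day 7 | A score too early for week 2, and no stated further follow-up |

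For reason (4) the discontinuation visit itself may be hard to achieve, since the reason is that examination has become difficult.

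**Step 3. What the test does.** A t-test on change needs a week-2 value. A patient without one contributes nothing unless a rule supplies a value. If 'initial information' means a baseline score, the patient stays in the set but is dropped by the test. If it means a first score on treatment, a patient with no such score is dropped by the set.

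**Step 4. Size.** Let *m* be the share of an arm with no week-2 score, and *g* the mean change in observed patients minus that in unobserved patients. The arm mean is then off by *m* × *g*, and the treatment difference by *m*(N) × *g*(N) − *m*(M) × *g*(M), for naldemedine (N) and magnesium oxide (M). Equal *m* and equal *g* cancel.

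The documents give neither *m* nor *g*. As a scale only, **assume** loss in one arm alone and a gap equal to the planned difference of 0.43:

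| Assumed *m* in one arm | Shift in the difference |
|---|---|
| 5% | 0.05 × 0.43 = 0.022 |
| 10% | 0.10 × 0.43 = 0.043 |
| 15% | 0.15 × 0.43 = 0.065 |

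The sign depends on which arm loses patients and on whether those patients fared better or worse.

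Loss also costs power even without bias. At the stated difference and SD (exact t-test), power is 86.7% with 60 scores per group, 85.0% with 57, 83.0% with 54 and 80.8% with 51.

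**The case against.** The case against has several parts.

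- **The set is not a completer set by definition.** A reader might infer that 11.2 admits only patients with a week-2 score. It does not say so: if 'initial' means baseline, patients without week 2 remain members. This stands. Any such loss would then come from the test, and a rule for missing scores may be in an analysis plan that is not shown. The absence of that rule is no fault of the protocol.
- **Patients stopped for (4) to (6) are not simply abandoned.** Section 9.2.2 gives every discontinuing patient a questionnaire visit. This also stands. It narrows the gap to stops before about day 7, plus the unstated status of later discontinuation scores.
- **Diarrhea does not show that loss will differ by arm.** Section 8.4 quotes 21.9% on naldemedine and 1.1% on magnesium oxide, and a reader might turn these rates into loss rates. The documents do not support that. Grade 3 or worse events, poor compliance and patient request are all followed reasons; section 7.2 allows dose reduction as well as withdrawal; and 8.4 gives no time frame. What remains is that a physician-led withdrawal for milder diarrhea could fall under (6). That is a possible route to unequal loss, with no known frequency.
- **Budgeting for dropout is ordinary practice.** Going from 51 to 60 is not evidence of bias. No rate is stated, and the allowance is not tied to week 2 rather than week 12. It would be wrong to read it as a forecast that 15% will lack the primary outcome.

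None of this removes the mismatch between label and definition, or the fact that continued observation depends on the reason for stopping.

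**Conclusion.** The point holds in a limited form. The intention-to-treat label does not fit a set that requires dosing and an undefined piece of endpoint information. Section 7.3 secures continued observation for three of six discontinuation reasons. For the other three, the only provision is a discontinuation-visit score whose standing as a week-2 value is not stated. The patients at risk of having no primary outcome are those never dosed and those who stop early, before about day 7, for reasons (4) to (6).

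The size and direction of any bias cannot be derived from the documents. The shifts of 0.022 to 0.065 shown above rest wholly on assumed loss rates and an assumed gap, and they are not estimates. If early stops of this kind are rare or balanced between arms, the effect is negligible. The reason to act is that the gap is cheap to close before data are collected and cannot be closed afterwards. This is an improvement that should be made; it does not show that the primary result would be invalid.

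**What to change.** 1. **11.2, set:** define the primary efficacy set as all randomised patients analysed by assigned arm. If the dosing requirement is kept, drop the intention-to-treat label.
2. **11.2, wording:** say what 'initial information' means (baseline score or first score on treatment), or remove the phrase.
3. **7.3, follow-up:** state that the week-2 and week-12 JPAC-QOL will be sought after every discontinuation reason, by post or telephone if needed, unless the patient withdraws consent to follow-up. This concerns data collection only and leaves the rules for stopping treatment as they are.
4. **9.2.2, timing:** state whether a discontinuation-visit score inside the week-2 window (±7 days) counts as the week-2 value, and how an earlier one is treated.

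The choice of model for incomplete data and any sensitivity analysis for missing scores can be left to the statistical analysis plan.

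The cost is a few sentences and a few extra posted or telephoned questionnaires, with some added burden on patients who have already stopped treatment.

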## 6.4 Method of randomization

Eligible patients will be randomly assigned (1:1) to receive 500 mg magnesium oxide thrice daily, or 0.2 mg naldemedine once daily at the central registration center. Randomization will be carried out after the patient has signed the informed consent form. To avoid a large bias, we will stratify age ( $<65$ ,  $\geq 65$ ) and gender (male, female) using computer-generated administered procedure, in permuted-block method.

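### The primary test in section 11.2 is valid but unadjusted: it leaves out baseline JPAC-QOL and the stratification factors as covariates and so gives up precision of uncertain size

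*Protocol*

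**What the plan says.** The primary endpoint (Protocol 10.1) is "The change in JPAC-QOL from baseline at 2 weeks". Section 11.2 names the primary analysis: "one-way analysis of variance across the 2 groups will be performed with calculating the p-value using the" Student's t-test, at a two-sided 5% level, with p-value and confidence intervals both used to judge significance. It lists no covariate, no stratum term and no adjusted sensitivity analysis. Section 11.1 sizes the trial for the same unadjusted F-test.

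Section 6.4 describes 1:1 randomisation with stratification: "To avoid a large bias, we will stratify age" (under 65, 65 and over) and "gender (male, female) using computer-generated administered procedure, in permuted-block method". The schedule in section 9.3 requires JPAC-QOL at baseline, week 2 and week 12, so the natural covariate is collected in any case.

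**The concern.** One-way ANOVA with two groups is the two-sample t-test, so treatment is the only term in the primary model. Three things follow.

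- **Precision.** A change score subtracts baseline with a fixed coefficient of 1. Unless the regression slope of week-2 score on baseline is 1, change stays correlated with baseline, and variance that a covariate could remove stays in the error term.
- **Chance imbalance.** For the same reason, a chance difference between arms in baseline JPAC-QOL is only partly corrected. Eligibility (5.1, 5.2) neither requires nor rules out existing constipation as such, so baseline scores may vary widely, although the protocol gives no spread.
- **Strata.** Stratification makes the arms more alike on age and gender. If these predict change, a model that omits them overstates the standard error; the interval is then too wide and the test somewhat conservative.

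At stake is the power and interval width of the primary comparison.

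**Working it through.** **Inputs from the protocol (11.1).** Mean changes: "naldemedine group and magnesium oxide group to be -1.19 and -0.76, respectively", a difference of 1.19 − 0.76 = 0.43. SD of change: "with a common standard deviation of 0.76". Two-sided 5%. Stated result: "51 patients are needed in each group to reach 90% statistical power".

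**Inputs that are assumed.** The protocol does not give rho, the correlation between baseline and week-2 JPAC-QOL, or k, the ratio of week-2 SD to baseline SD. I take rho = 0.3, 0.5, 0.7 and k = 0.8, 1, 1.25, 1.5.

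**Step 1: the plan's own figure.** n per arm = 2 × [0.76 × (1.960 + 1.282) / 0.43]² = 65.6, so 66; the t-test calculation gives 67. The stated 51 is not reproduced. Unadjusted t-test power is 80.8% at 51 per arm and 86.7% at 60. This is the starting point for the comparison and is a separate fault in 11.1.

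**Step 2: effect of a baseline covariate.** With baseline SD equal to s:

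- Var(change) = s²(1 + k² − 2·rho·k)
- Var(ANCOVA residual) = s²k²(1 − rho²)
- Ratio = k²(1 − rho²) / (1 + k² − 2·rho·k) = 1 − (1 − rho·k)² / (1 + k² − 2·rho·k)

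The ratio never exceeds 1, so in large samples the adjusted analysis is never less precise. It equals 1 when rho·k = 1, where nothing is gained. With k = 1 it reduces to (1 + rho)/2.

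Effective SD is 0.76 × √ratio. Power for 0.43 at 51 per arm (noncentral t, ignoring the few degrees of freedom spent on covariates):

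| k | rho | ratio | effective SD | power |
|---|---|---|---|---|
| unadjusted | – | 1 | 0.760 | 80.8% |
| 0.8 | 0.3 / 0.5 / 0.7 | 0.502 / 0.571 / 0.628 | 0.539 / 0.575 / 0.602 | 97.9% / 96.3% / 94.6% |
| 1 | 0.3 / 0.5 / 0.7 | 0.650 / 0.750 / 0.850 | 0.613 / 0.658 / 0.701 | 93.9% / 90.4% / 86.6% |
| 1.25 | 0.3 / 0.5 / 0.7 | 0.784 / 0.893 / 0.981 | 0.673 / 0.718 / 0.753 | 89.2% / 85.0% / 81.5% |
| 1.5 | 0.3 / 0.5 / 0.7 | 0.871 / 0.964 / 0.998 | 0.709 / 0.746 / 0.759 | 85.8% / 82.2% / 80.9% |

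The 95% interval half-width at 51 per arm, 1.96 × SD × √(2/51), is 0.295 unadjusted. With k = 1 it is 0.238, 0.255 and 0.272 for rho 0.3, 0.5 and 0.7.

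At 60 per arm with k = 1, adjusted power is 96.8%, 94.4% and 91.5%, against 86.7% unadjusted.

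**Step 3: chance baseline imbalance.** Take k = 1 and rho = 0.5. Then s = 0.76 / √(2 × 0.5) = 0.76, and the slope of change on baseline is 0.5 − 1 = −0.5. One standard error of the baseline difference at 51 per arm is 0.76 × √(2/51) = 0.151. An imbalance of that size moves the unadjusted estimate by 0.5 × 0.151 = 0.075, or 17.5% of 0.43.

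**Step 4: strata alone.** If age group and gender explain an assumed 2% to 10% of the variance of change, adjusting for them raises power at 51 per arm from 81.5% to between 82.3% and 85.4% (normal approximation). Leaving them out gives the nominal 5% test an actual level of about 4.8% to 3.9%.

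**The case against.** The strongest reply is that nothing here is an error. Under 1:1 randomisation the difference in mean change is unbiased on average, omitting prognostic strata makes the test conservative, and sections 10.1, 11.1 and 11.2 agree with one another. That stands: the point concerns efficiency.

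A reader might infer that the test ignores baseline altogether. It does not: change subtracts baseline for each patient, and baseline is absent only as a covariate.

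A reader might also infer that ANCOVA restores the 90% power claimed in 11.1. The protocol does not support this. At 51 per arm it would need rho of about 0.5 or lower with equal SDs. Patients are opioid-naive at baseline and then start opioids, so a wider spread at week 2 is plausible though not stated; at k = 1.5 and rho = 0.7 the gain is nil. The 81% also comes from the miscalculation in 11.1 and not from the choice of test.

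Finally, nothing in the protocol shows that age group or gender predicts change in JPAC-QOL. The strata effect in step 4 is therefore conditional, and it is small.

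None of this gives a reason to prefer the unadjusted model. Adjustment costs almost nothing and in large samples cannot lose precision.

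**Conclusion.** The point holds as a recommendation to improve precision. The protocol itself commits to an unadjusted primary test while collecting baseline JPAC-QOL and stratifying on two factors that the test leaves out. The planned test is valid, and conservative if the strata are prognostic.

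The gain is indeterminate. Against 81% unadjusted at 51 per arm, baseline adjustment gives anything from no material gain to about 98% over the assumed ranges of rho and k. Most of any gain would come from baseline; the strata add about 1 to 4 points under the assumed 2% to 10% of variance. The figures rest on the protocol's 0.43 and 0.76, which it takes from a retrospective series of 10 patients.

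**What to change.** In section 11.2, make the primary analysis an ANCOVA of week-2 change in JPAC-QOL on treatment, baseline JPAC-QOL, age group (<65, ≥65) and gender. Report the adjusted mean difference with its 95% confidence interval, and keep the unadjusted t-test as a sensitivity analysis. Fix the covariates before outcomes by arm are examined.

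The cost is one sentence and three degrees of freedom, with no new data, visits or patients, and the named JMP software can fit the model. Section 18 limits minor changes to those unrelated to the primary endpoints, so the edit probably needs Ethics Committee approval as a major change.

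Correct the sample-size statement in 11.1 separately. It should not be left standing on the strength of an adjustment whose benefit the protocol cannot quantify.

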### 11.3 Interim Analysis

Not applicable.

## 12. Case Report Forms

Contents: Collection period

Case registration form: at the time of case registration

Start ~ end of protocol treatment: within 14 days after the end of protocol treatment

At the time of discontinuation: within 1 week of visit

### **13. Efficacy and Safety Evaluation Committee**

The purpose of this committee is to ensure the proper conduct of the study and to reduce the burden on subjects as much as possible. The committee will make decisions whether or not to continue the study from the perspective of safety and efficacy. In the event of death or serious adverse events, the committee will decide whether there is a causal relationship and whether appropriate measures were taken. The committee members in charge will be those who have no conflict of interest with the study and will perform their duties from an objective standpoint.

Effectiveness and Safety Evaluation Committee meeting will be held via email or Skype. When an unknown adverse event occurs, the committee will respond in accordance with the separately established procedures.

### **14. Ethical issues**

#### **14.1 Ethical Conduction of Study**

The study will be performed in accordance with the Declaration of Helsinki and the Japanese ethical guidelines for clinical research. The physician in charge will conduct the study in compliance with this protocol. If deviations or changes are made from the protocol in order to avoid immediate danger to the subject or for other unavoidable medical reasons, the reasons will be recorded in the medical record and case report form. If the deviation or change is critical to the continuation of the study, the principal investigator and the Efficacy and Safety Evaluation Committee will consider stopping the study or changing the study plan.

#### **14.2 Handling of Personal Information**

The principal investigator or co-investigator will assign an identification code to the patient. The identification code will not contain information that can identify the individual study subject, such as the subject's medical record ID or name. A correspondence table that can identify the subjects from the identification codes will be made to identify or refer to the subjects, but it will not be provided outside the study institution. Even when the results of this study are made public, they will not contain the subjects' personal information.

### **15. Patient Informed Consent and Information Provision**

Before the patient participation, the physician in charge will fully explain the following items using the informed consent form approved by the Ethics Committee of the institution. After confirming that the patient fully understands the contents, consent for

participation will be obtained in writing.

In principle, the items to be explained to the subjects will be as follows (this shall not apply to things approved by the hospital director based on the opinion of the Ethical Review Committee);

1. That the study permission has been obtained.
2. Study period and principal investigator
3. Purpose and significance of the study
4. Method and duration of the study
5. Reasons for selection as study subjects
6. Burden and anticipated risks and benefits
7. That the subject can withdraw the study.
8. That the subject will not be disadvantaged.
9. About other treatment methods
10. Access to materials
11. Handling of personal information
12. Methods of storage and disposal of samples and information
13. Conflict of interest
14. Consultation with study subjects and related parties
15. About expenses
16. Provision of medical care after the study is conducted
17. Handling of incidental findings
18. Compensation for health damage
19. Possibility of future study
20. Access to samples and information by concerned parties
21. Publication of study results
22. Intellectual property rights

